### Interim analyses {21b}

N/A. On the basis of previous observation and clinical practice experience, we judge that there will be no high-grade adverse events during the study; therefore, we have not set an interim analysis.

### Methods for additional analyses (e.g., subgroup analyses) {20b}

N/A. In this study, there are just two groups including FSM group and SM group, with no subgroups set up within the two groups. As a result, there is no additional analysis.

### Methods in analysis to handle protocol non-adherence and any statistical methods to handle missing data {20c}

All analyses will be based on the intention-to-treat principle. For instance, data for all participants will be analyzed in accordance with the randomized treatment assignment, even if there are cases of protocol non adherence. Since outpatient appointments are made for each treatment and follow-up, and participants can always contact the investigators for any advice they need, there will not be much missing data. When the case is dropped or the patient’s compliance is poor, the reasons for the drop or poor compliance must be detailed in the case observation form, and the patient’s understanding and support must be obtained by contacting the patient as frequently as possible. The case drop-off, patient compliance, and adverse reactions must be statistically described, compared, and analyzed among groups.

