### Criteria for discontinuing or modifying allocated interventions {11b}

Participants may request to withdraw the study or be withdrawn because of study-related adverse events and withdrawal criteria. If a participant withdraws from the study, the study assistant will interview them about their reasons for leaving and collect their safety data, all of which will be recorded in detail in the case report forms (CRFs). If a participant experiences an adverse event and discontinues the study, the clinician will evaluate the patient’s condition to determine if additional treatment is needed.

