### Sample size {14}

The sample size is calculated based on our preliminary study, which was completed from November 2021 to February 2022. The prior research compared CMS changes from baseline to the end of 4-week treatment in patients receiving FSM or SM plus home-based exercise. Our previous results showed that CMS increased by 24.32 (μ_r_) in the FSM group and increased by 10.31 (μ_c_) in the SM group, and the standard deviation of the FSM group was 17.84 (*σ*). On the basis of the above data, when 1/3 of the standard deviation of the FSM group is selected for Δ, *α* = 0.025 (single-sided), *Z*_1−0.025_ = 1.96, 1 – *β* = 0.90, *Z*_1−0.10_ = 1.282, and the ratio of the number of subjects between the FSM group and SM group (*K*) = 1, using the following formula, 104 participants are required for each group: $${n}_{c}=\frac{{{\left({Z}_{1-\alpha }+{Z}_{1-\beta }\right)}^{2}\sigma }^{2}\left(1+\frac{1}{K}\right)}{{\left({\mu }_{r}-{\mu }_{c}-\Delta \right)}^{2}}$$$${n}_{r}={Kn }\ _{c}$$

On this basis, considering an estimated dropout rate of 20%, 125 cases will be needed for each group. Additionally, because there are three trial centers in this study, 15 additional cases are required for each group owing to the multicenter design. Therefore, a total of 280 participants will be enrolled in this study, with 140 participants in both the FSM group and the SM group.

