## Statistical methods

### Statistical methods for primary and secondary outcomes {20a}

SPSS V26 (IBM Corp., Armonk, NY, USA) will be used for both data input and analysis. Statistical analysis will be performed as follows. First, descriptive statistics will be used for all outcome measures at each measurement point to summarize the results. For normally and nonnormally distributed measurement data, the mean ± standard deviation, and median, will be used for the statistical description of the degree of trend, and dispersion, respectively. Second, differences in the mean change in primary and secondary outcomes from baseline to each time point between the groups will be compared using two independent samples *t*-tests or the Mann–Whitney *U*-test. Finally, chi-square tests will be used for blind evaluation. Statistical significance will be set at a *p*-value < 0.05 (two-sided). Table 3 summarizes the statistical analysis of primary and secondary outcomes.

**Table 3 Tab3:** Variables, measures, and methods for statistical analysis of primary and secondary outcomes

Variable/outcome	Outcome measure	Methods of analysis
1) Primary		
The mean of change in shoulder function from baseline to 4, 12, 18, and 24 weeks	Constant-Murley score (continuous)	*T*-test or Mann–Whitney *U*-test^a^
2) Secondary		
The mean of change in shoulder pain from baseline to 4, 12, 18, and 24 weeks	Visual analogue scale (continuous)	*T*-test or Mann–Whitney *U*-test^a^
The mean of change in shoulder range of motion from baseline to 4, 12, 18, and 24 weeks	Active range of movement of shoulder joint (continuous)	*T*-test or Mann–Whitney *U*-test^a^
The mean of change in quality of life from baseline to 4, 12, 18, and 24 weeks	The 36-Item Short Form Survey (continuous)	*T*-test or Mann–Whitney *U*-test^a^

^a^For data conforming to normal distribution, *T*-test is used, and for data not conforming to normal distribution, Mann–Whitney *U*-test test is used

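### Section {20c} claims intention-to-treat on all participants and expects little missing data, but 20% dropout is planned and the per-visit tests, as written, use only participants seen at that visit

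*Protocol article*

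**What the plan says.** Four parts of the protocol article bear on this point.

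- **Population and missing data, section {20c}.** All analyses are to follow intention-to-treat: "data for all participants will be analyzed in accordance with the randomized treatment assignment". On missing data the section gives an expectation, "there will not be much missing data", and supports it by the appointment system and patients' access to the investigators. It also asks for contact with patients who drop out or comply poorly, and for drop-out to be described and compared between groups.
- **Expected loss, section {14}.** The sample size is inflated for loss: "considering an estimated dropout rate of 20%, 125 cases will be needed for each group".
- **Analysis, section {20a} and Table 3.** The plan is that "differences in the mean change in primary and secondary outcomes from baseline to each time point between the groups will be compared". The test named is a t-test or, where the data are not normal, a Mann–Whitney test. This applies at weeks 4, 12, 18 and 24. Table 1 puts the principal CMS analysis at weeks 4 and 12.
- **Withdrawal, section {11b}.** When a participant withdraws, "the study assistant will interview them about their reasons for leaving and collect their safety data".

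**The concern.** Two statements conflict. A trial that budgets for one participant in five dropping out cannot also rest its approach to missing data on there being little of it. And a promise to analyse everyone as randomised is not delivered by a two-sample test on change at a single visit, because that test needs a score at that visit. As written, each of the four comparisons runs on whoever attended, possibly a different subset each time. It also ignores those participants' other visits, their baseline CMS as a covariate, and the centre by which randomisation is stratified (section {16a}).

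The stake is bias. Section {22} gives worsening pain and progressing dysfunction as examples of adverse events, sections {17b} and {22} let the monitoring committee decide on discontinuation after an adverse event, and section {11b} allows withdrawal for study-related adverse events. Pain and function are also what the CMS measures. Loss related to the outcome is therefore plausible. Since one arm receives active manipulation and the other an inert sham, the loss may differ between arms. A CMS value not collected after withdrawal cannot be recovered at analysis.

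**Working it through.** **Inputs (section {14}).** Mean CMS change 24.32 (FSM) and 10.31 (SM); SD 17.84; Δ = one third of the SD; one-sided α = 0.025 (z = 1.96); power 0.90 (z = 1.282); 1:1 allocation; dropout 20%; 140 enrolled per arm.

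**1. The plan's own figure.**
- Planned difference: 24.32 − 10.31 = 14.01. Δ = 17.84/3 = 5.947. Difference less Δ: 8.063.
- n per arm = 2 × 17.84² × (1.96 + 1.282)² / 8.063² = 102.9, so 103. The plan states 104; this reproduces within rounding.
- Dropout step: 104 × 1.2 = 124.8, so 125 as stated. Adding 15 per arm gives 140.

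**2. How many could be missing.**
- 0.20 × 280 = 56, or 28 per arm, leaving 140 − 28 = 112 per arm.
- Section {14} does not say when in the 24 weeks dropout occurs. At weeks 4 and 12, 56 is therefore an upper figure under the planning assumption.

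**3. Is power harmed?**
- Power = Φ(8.063 / (17.84 × √(2/n)) − 1.96).
- n = 112: 8.063/2.384 − 1.96 = 1.42, power 92.3%.
- n = 140: 8.063/2.132 − 1.96 = 1.82, power 96.6%.
- Loss of up to 1 − 104/140 = 25.7% still leaves the required 104 per arm. Power is not harmed at 20%.

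**4. Size of a possible bias (assumptions, not figures from the document).** Let a fraction f of an arm be missing, with a true mean change g points below that of completers. The arm's all-randomised mean is then the completer mean minus f × g, so the observed-only mean is too high by f × g.

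| f, one arm only | g (CMS points) | Shift in the difference | Share of 14.01 |
|---|---|---|---|
| 0.20 | 5 | 1.0 | 7% |
| 0.20 | 10 | 2.0 | 14% |
| 0.20 | 14.01 | 2.8 | 20% |

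The last row is the case in which the missing FSM participants improved only as SM participants do: the all-randomised effect would be 0.8 × 14.01 = 11.2. The shift favours FSM if the gap is in the FSM arm and works against it if the gap is in the SM arm. With gaps in both arms the net shift is the difference of the two products, so similar gaps and fractions largely cancel.

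**5. What is collected after withdrawal.** Section {11b} names reasons for leaving and safety data. Section {20c} asks for repeated contact with patients who drop out, but in order to record reasons and gain their understanding and support. Neither these nor any other section of the article provides for a CMS assessment after withdrawal.

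**The case against.** The strongest reply is that this is a journal article. An imputation rule or a sensitivity analysis may sit in a full protocol or analysis plan that is not shown, and naming a t-test does not by itself exclude participants with missing values, since imputation could come first. The sentence in {20c} on analysis by randomised assignment is explained there in terms of non-adherence, that is, of arm assignment. What stands of this: the mere absence of an imputation method is no finding. But {20c} does more than stay silent. It offers an expectation that {14} contradicts, while {20a} and Table 3 fix the tests. Nothing in the article suggests that imputation precedes them.

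Retention is also taken seriously: visit reminders ({11c}), a transport subsidy ({18b}), free FSM for the sham arm at the end ({30}), and contact with patients who drop out ({20c}). These may hold loss below 20%, but they do not reconcile the two sections.

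Three stronger readings are tempting and are not supported:

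- *Only safety data are collected after withdrawal.* Section {11b} also records reasons for leaving, does not bar outcome follow-up, and concerns leaving the study, not merely missing sessions.
- *56 participants leave the primary analysis.* The timing of dropout is not given, and a missed visit removes a participant from that visit's comparison, not from every analysis.
- *The bias is up to a third of the superiority margin.* That arithmetic uses the Δ of 5.95 from the sample size, but {20a} tests at two-sided p < 0.05 without applying a margin. The planned difference of 14.01 is the fairer yardstick.

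Finally, a mixed model is no complete cure. It assumes missing at random and omits anyone with no post-baseline value. That is correct, and the fix has to say so.

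**Conclusion.** The point holds as an internal conflict with a moderate, conditional consequence. Section {20c} expects little missing data where {14} plans for 20%. The per-visit tests in {20a}, as written, do not deliver the all-participants analysis that {20c} claims, and CMS follow-up after withdrawal is not provided for. Power is adequate at the planned loss (about 92% with 112 per arm).

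The possible bias is 1 to 2 CMS points, 7 to 14% of the planned difference. This assumes 20% missing in one arm, a gap of 5 to 10 points between dropouts and completers there, and no such gap in the other arm. The article gives no source for such a gap, so the figures show scale and do not predict a result. They do not show that the trial's conclusion would change. Severity: should fix.

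**What to change.** 1. **Sections {20a} and Table 3.** Make the primary analysis of CMS change one mixed model for repeated measures over weeks 4, 12, 18 and 24, with treatment, visit, treatment-by-visit, baseline CMS and centre. Include all randomised participants with any post-baseline value, and read the principal contrasts at weeks 4 and 12. State that the model assumes missing at random.
2. **Section {20c}.** Add a delta-adjusted sensitivity analysis that also covers participants with no post-baseline value, so that every randomised participant enters at least one analysis and departures from missing at random are examined.
3. **Section {11b}.** State that scheduled CMS assessments continue after a participant stops the intervention, unless consent is withdrawn. This concerns data collection only, not when treatment should stop.
4. **Section {20c}.** Replace the expectation of little missing data with the 20% planning figure from {14}.

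**Cost.** Changes of wording, modest extra analysis work (the planned SPSS can fit the model), and follow-up effort at visits that are already scheduled. No change to the sample size is needed for this point. The third item is the urgent one, because it has to be in force while participants are still being followed.

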### Plans to give access to the full protocol, participant-level data, and statistical code {31c}

The protocol for this study is publicly available at China Registered Clinical Trial Registration Center (ChiCTR2000037577). At the end of the study, the data and analysis results will be available from the corresponding author upon reasonable request.

## Oversight and monitoring

### Composition of the coordinating center and trial steering committee {5d}

The trial steering committee, comprising the senior supervisor and the directors of each center, will be responsible for monitoring and coordinating the research and providing day-to-day support. The research group will conduct monthly inspections to follow the progress of the research and ensure that the trial process is standardized.

### Composition of the data monitoring committee, its role, and reporting structure {21a}

This study will designate a DSMC consisting of an orthopedic surgeon, ethicist, and a statistician and an assistant, who will be independent of the study. To ensure the quality and safety of the study, the DSMC will check the manipulation technique, CRFs, patient safety, data quality, and the descriptions of withdrawals or study dropouts every 2 weeks.

### Adverse event reporting and harms {22}

The safety of the participants will be monitored by the DSMC throughout the study. After each manipulation session and at each follow-up, the study assistant will ask the participants if there are any adverse events, such as worsening pain or progression of dysfunction, and record these events (if any) in detail. Adverse events will be reported to the DSMC, who will determine whether the participant needs to be discontinued and unblinded immediately.

### Frequency and plans for auditing trial conduct {23}

The Ethics Committee of Shanghai Municipal Hospital of TCM will conduct an audit of the study every 3 months to understand the progress, safety, and authenticity of the data and whether there are ethical violations. The members of the ethics committee are independent of the investigators and the sponsor.

### Plans for communicating important protocol amendments to relevant parties (e.g., trial participants, ethical committees) {25}

Any modification to the study protocol will be reported to the Ethics Committee of Shanghai Municipal Hospital of TCM for re-approval. If the modified content has any impact on the patients, the patients will be informed and requested to provide signed informed consent again. At the same time, registration changes will be synchronized.

### Dissemination plans {31a}

Whether the results are positive or negative, we will publish them in the peer-reviewed journal.

## Discussion

RCRSP is a growing worldwide health problem that causes shoulder pain and completely or partially stiffness. Increasing evidence has shown that dynamic constriction of the subacromial space with compression of the subacromial soft tissues is considered to be the key cause of chronic RCRSP [21–23]. Patients with RCRSP usually have tight shoulder muscles and joint capsule, which, in turn, may cause abnormal kinematics of the humerus, scapula, and clavicle, resulting in narrowing of the subacromial space and compression of the soft tissue through it. Therefore, the restoration of subacromial space stenosis is a therapeutic goal for RCRSP treatment. Anatomically, the activity of the shoulder joint includes the coordination of glenohumeral, scapothoracic jiont, sternoclavicular, and acromioclavicular four joints [24]. Previous studies have proven that manipulation therapy can effectively promote the rehabilitation of RCRSP, implying that manipulation is an alternative treatment for RCRSP [25, 26]. Despite the fact that the obvious therapeutic modalities predominantly include glenohumeral or scapulothoracic joint mobilization, spinal manipulation, and soft tissue release [26], we created the FSM to address four joints associated with shoulder motion, trying to quickly regain joint coordination and relieve subacromial soft tissue compression. We hypothesize that individuals using FSM will achieve faster improvements in symptoms and functional limitations compared with those who receive the sham manipulation. Therefore, a randomized, participant-, outcome assessor-, and data analyst-blinded, placebo-controlled study is required to confirm the efficacy of FSM in treating RCRSP.

In clinical trials, a placebo as a control treatment not only effectively evaluates the effectiveness of the treatment tested but also facilitates the implementation of blinding and eliminates several potential biases, such as patients’ dependence on therapists and expectations of treatment efficacy [27–29]. In manipulative studies, it is impossible to blind the therapist; therefore, using an inert manipulative therapy as a placebo to blind the participants is the best alternative. Previous studies have demonstrated the reliability of using SM as a placebo in manipulative studies [15, 30]. In this study, the inert treatment effect is achieved by applying no thrust and strictly confining the manipulation to the skin surface in accordance with the procedure tailored to FSM. In this study, the participants will be treated individually at different times to avoid communication and interference between participants. We hope to minimize potential differences by implementing the above interventions.

The main symptoms of RCRSP are pain, dysfunction, and loss of strength, and therefore a comprehensive evaluation tool is appropriate for the primary outcome. The evaluation content of the CMS basically covers all the symptoms of RCRSP and the adverse effects on quality of life, with good validity and responsiveness. Because the CMS is used widely in the assessment of shoulder diseases [31], we chose this measurement tool as the primary outcome of the study. Additionally, we will use VAS scores, ROM, and SF-36 scores to accurately quantify pain, function, and quality of life, respectively.

To provide a more accurate assessment, we intend to conduct this well-designed RCT to investigate both the efficacy and safety of RCRSP, contributing to worthy clinical evidence for manipulative therapy in RCRSP.

## Trial status

Recruitment is scheduled to begin on 1 July 2022, and the study will continue until 31 December 2023. The current protocol is version 2.0, June 19, 2022.

## Data Availability

At the end of the study, the data and analysis results will be available from the corresponding author ([name]) upon reasonable request.

## Abbreviations

RCRSP: Rotator cuff–related shoulder pain
FSM: Five-step shoulder manipulation
SM: Sham manipulation
CMS: Constant-Murley score
VAS: Visual analog scale
ROM: Range of motion
SF-36: 36-Item Short Form Survey
TCM: Traditional Chinese medicine
DSMC: Data and safety monitoring committee
CRF: Case report form
